#### Secondary outcomes

See secondary objectives for an overview of objectives and their derived outcomes.

Our hypothesis is that the T2T continuation ULT strategy is superior at the group level in ULT using gout patients in remission. However, this advice might be personalized. Potential predictors, including clinical, immunological, (epi)genetic and imaging variables collected during the GO TEST Finale study, are studied as potential effect modifiers. This will be done by exploratory prediction modelling using logistic and cox regression modelling including all candidate predictors, thereafter, followed by the development of a prediction model and subsequent internal validation using k-fold cross-validation.

To investigate the cost-effectiveness of both treatment strategies, the costs of either approach is calculated and will be compared with each other. Current medication use (type, dosage, frequency and administration route) will be recorded and updated at each clinic visit. Costs of medication use will be derived from the Dutch formulary and increased with a pharmacist charge. Self-reported healthcare resource usage and productivity loss will be assessed using questionnaires administered at baseline and then three monthly until the study end at 24 months. Medical consumption will be assessed using the iMTA Medical Consumption Questionnaire (iMCQ) and productivity loss will be assessed by using the iMTA Productivity Cost Questionnaire (iPCQ). Cost prices will be calculated according to the 2016 Dutch guideline for health economic evaluation [29]. A friction cost will be applied to estimate the productivity losses as defined in the Dutch costing manual, and based on the reference costs of being unable to perform paid or unpaid work.

Incremental cost-effectiveness ratios (ICER) will be calculated with credible intervals using bootstrapping. Incremental net monetary benefit (iNMB) will be estimated based on different levels of willingness-to-pay (WTP).

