#### Secondary objectives

To exploratory assess non-inferiority (only when superiority cannot be demonstrated) of the treat-to-symptom strategy compared to the treat-to-target strategy.To assess the between-group difference in the incidence (cumulative incidence and incidence density) of gout flares during the follow-up period of 24 months according to gout flare criteria [23].To assess the proportion of participants that require reintroduction of ULT in the T2S discontinuation strategy group.To assess the between-group difference in the use of ULT and gout flare medication (anti-inflammatory medication).To assess predictors for successful ULT cessation in the T2S discontinuation strategy group including clinical, radiological, immunological, and genetic variables.To evaluate the between-group difference in Patient-Reported Outcome Measures, by three monthly analysing the 5-level EuroQol-5 domains (EQ-5D-5L) questionnaire, functioning by using the Health Assessment Questionnaire Disability Index (HAQ-DI), numeric rating scale (NRS) for pain and NRS global health.To assess the between-group difference in types and frequency of adverse events, with a special focus on change in the renal function defined by Glomerular Filtration Rate Chronic Kidney Disease – Epidemiology Collaboration (GFR-CKD-EPI) and incidence of major adverse cardiovascular events (defined as arrhythmia, non-fatal stroke, non-fatal myocardial infarction, (hospitalization for) acute coronary syndrome, cardiovascular hospitalizations and cardiovascular death) during the follow-up period of 24 months. For the MACE there is a special interest in the first 3 to 6 months after ULT cessation and reintroduction of ULT in the T2S group.To assess the (between-group) difference in prescribed medication compared with refill rates during the follow-up period of 24 months.To assess the incremental cost-effectiveness of a T2T ULT continuation strategy compared to a T2S ULT discontinuation strategy.

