### Sample size {14}

The null hypothesis is that no statistical difference is found between the continued T2T approach and the T2S discontinuation approach. Since the T2S group receives less intensive treatment, the superiority of the T2S discontinuation approach in terms of efficacy is considered unlikely and also irrelevant. After all, one would prefer the less intensive treatment as long as the more intensive treatment is not clearly superior, regardless of whether the less intensive treatment is equally effective or superior. Therefore, we use a one-sided test to achieve the same power to show the superiority of continued T2T with a smaller study size compared to a two-sided test with the same alpha.

Based on earlier studies and on unpublished data from our own cohort (2400 gout patients from Sint Maartenskliniek, Radboudumc and Rijnstate) we estimate that 8% of gout patients following the treat-to-target strategy experience at least 1 gout flare during the 2-year follow-up and 4% of patients are not in remission in the last 6 months of the 24-month follow-up. For the patients in the treat-to-symptom group, less data is available, but we estimate that 12% are not in remission in the last 6 months of the follow-up time, based on the 5 smaller cohort studies included in the review of Beslon et al [11].

Using alpha 0.05, power 1-beta 0.80, one-sided superiority testing with a two proportion *z* test, and expected proportion of patients not fulfilling the adapted preliminary remission criteria for gout domains during the last 6 months of the study of 0.04 and 0.12 in the T2T strategy and control group T2S strategy (difference 0.08, number needed to harm, number needed to harm, NNH, 12), 278 analysable patients are needed. Accounting for 10% dropout, 310 patients will be included. If during follow-up dropout turns out to be lower (based on incidence density of dropout/patient-years), fewer patients will be included.

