### Methods for additional analyses (e.g. subgroup analyses) {20b}

Not applicable.

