## Discussion

With this multicentre, randomized, superiority trial, we aim to investigate whether a continued T2T strategy with ULT is superior compared to a trial and error T2S discontinuation strategy for gout patients, who are in remission while using ULT. We would like to highlight and discuss some aspects of the design in more detail below.

First, our hypothesis is superiority on the group level of a ULT T2T continuation strategy compared to switching to a ULT discontinuation T2S strategy in gout patients in remission. The review by Beslon et al [11] showed a wide range of gout flare relapse rates in different cohort studies. Possible predictive factors (all not statistically significant) for unsuccessful ULT discontinuation (defined as recurrence of gout) were: higher serum urate levels before and after ULT treatment, higher body mass index (BMI), onset of gout at a young age and longer duration of ULT treatment. Another prospective cohort study found low serum urate levels while using ULT (<0.30 mmol/l or <5.05 mg/dl) and after ULT cessation (<0.51 mmol/l or <8.75 mg/dl), were significantly associated with the longest period of gout-free remission [32]. This led to the suggestion that an intermittent ULT strategy might work for some gout patients. Potential predictors including clinical, immunological (epi)genetic and imaging variables will be studied as effect modifiers to explore if personalized treatment advice can be given.

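### The protocol promises effect modifiers for personalised advice, but the predictor analysis it describes is confined to the T2S arm and can only give prognostic factors (minor)

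*Protocol article*

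**What the plan says.** Four places in the protocol article bear on this.

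- **Outcomes {12}, Secondary outcomes.** After saying that advice might be personalised, the text continues: "Potential predictors, including clinical, immunological, (epi)genetic and imaging variables collected during the GO TEST Finale study, are studied as potential effect modifiers". The method given is "exploratory prediction modelling using logistic and cox regression modelling including all candidate predictors", then development of a prediction model and k-fold cross-validation. No arm is named here, but the section refers the reader to the secondary objectives.
- **Discussion.** The same families of variables "will be studied as effect modifiers to explore if personalized treatment advice can be given".
- **Secondary objectives, and Statistical methods {20a}.** The only predictor objective is "To assess predictors for successful ULT cessation in the T2S discontinuation strategy group". The matching item under {20a} is also limited to the T2S group and uses exploratory regression for failed withdrawal of ULT.
- **Methods for additional analyses {20b}.** The answer, under a heading that names subgroup analyses as its example, is "Not applicable".

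**The concern.** An effect modifier is a feature across which the T2T-versus-T2S contrast changes. Estimating it needs outcomes from both arms at each level of the feature. Failed withdrawal has no counterpart in patients who continue ULT, and a model fitted in T2S patients contains no treatment contrast. Such a model can identify prognostic factors after stopping, but not who benefits from continuing.

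At stake is how the personalised-advice result is read. A feature that raises the risk of non-remission to the same extent under both strategies would appear as a predictor of failed cessation. It could then be taken as a reason to continue ULT in patients who gain no more from continuing than others do.

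A second, smaller matter is that all candidates are to be entered in a model that may have few events.

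**Working it through.** **1. Inputs (Sample size {14}, Introduction).** The design is stated as "Using alpha 0.05, power 1-beta 0.80, one-sided superiority testing with a two proportion *z* test". For T2T, "4% of patients are not in remission in the last 6 months of the 24-month follow-up"; for T2S, "we estimate that 12% are not in remission in the last 6 months of the follow-up time". The analysable total is 278, or 139 per arm at 1:1. The relapse range cited after stopping ULT is 36% to 81%. The number of candidate predictors is not given; 5, 10 and 20 are assumed below.

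**2. The plan's own figure.** With unpooled variance, n per arm = (1.645 + 0.842)² × (0.04 × 0.96 + 0.12 × 0.88) / 0.08² = 139.1, or 278 in total, as stated. The pooled form gives 142 per arm (284), within 3%. This figure serves the primary comparison; no sample size is given for the predictor work.

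**3. One arm against two (assumed stratum rates).** Take a binary feature present in half the patients.

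| | Feature absent | Feature present | Average |
|---|---|---|---|
| T2T | 1% | 7% | 4% |
| T2S | 9% | 15% | 12% |
| Difference | 8 points | 8 points | 8 points |

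The averages match the planning rates. The T2S odds ratio is (0.15/0.85) / (0.09/0.91) = 1.78, so a T2S-only model would flag the feature. The absolute gain from continuing is the same in both strata.

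If T2T risk is instead flat at 4% and T2S risk is 6% and 18%, the differences are 2 and 14 points, and T2S risk does order patients by benefit. Only T2T data can tell these two situations apart.

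**4. Information in the T2S model.** The definition of failed withdrawal is not given in the article, so three rates are shown for 139 patients. The limiting count is the smaller outcome class.

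| Assumed rate | Limiting count | Per candidate: 5 / 10 / 20 |
|---|---|---|
| 12% (primary outcome) | 16.7 events | 3.3 / 1.7 / 0.8 |
| 36% (low relapse figure) | 50.0 events | 10.0 / 5.0 / 2.5 |
| 81% (high relapse figure) | 26.4 non-events | 5.3 / 2.6 / 1.3 |

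**5. What a both-arm analysis could deliver.** Expected events for the primary outcome are 139 × 0.12 + 139 × 0.04 = 16.7 + 5.6 = 22.2. Assume a binary feature in half the patients (69.5 per cell), T2T risk 4% in both strata and two-sided 0.05. Approximate power = Φ(|effect|/SE − 1.96). On the log-odds scale the variance sums 1/[69.5 p(1 − p)] over the four cells. On the risk-difference scale it sums p(1 − p)/69.5.

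- T2S 4% and 20%: interaction odds ratio 6.0, SE 1.10, power 37%. Difference in risk differences 16 points, power 72%.
- T2S 6% and 18%: interaction odds ratio 3.4, SE 1.05, power 22%. Difference in risk differences 12 points, power 47%.

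**The case against.** The strongest reply is that the sentences on effect modifiers name no arm. The T2S restriction comes from the objectives and from {20a}, and the interaction terms may sit in the full protocol or a SAP that is not shown. That limits the claim. A reader might infer that the randomised T2T arm is being discarded for this question, but the article does not say so. What stands is that the article gives an aim and a method, and the only predictor analysis it describes cannot meet that aim.

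Three other strong readings are tempting and are not supported.

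- **That the advice would be wrong in direction for some patients.** In the example, continuing is better by 8 points in both strata. The example is also scale-dependent: the T2T odds ratio is (0.07/0.93) / (0.01/0.99) = 7.45, so the interaction odds ratio is 1.78/7.45 = 0.24. That is strong modification on the logistic scale. The document gives no stratum rates, and a low, flat T2T risk would make T2S risk a fair guide to absolute benefit.
- **That the T2S model will be overfitted.** Neither the number of candidates nor the outcome definition is stated. At 36% relapse and 5 candidates there are 10 events per candidate.
- **That a misleading performance figure would be reported.** In simulation with 139 patients, 17 events and pure-noise predictors, the apparent AUC is about 0.66, 0.73 and 0.82 for 5, 10 and 20 predictors. The five-fold cross-validated AUC is about 0.50 each time. The planned cross-validation would expose this if all fitting and selection are repeated inside the folds. It does not repair the coefficients, and no shrinkage is stated.

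It is also fair to say that a both-arm analysis is short of events. That argues for a very short list and cautious reporting; it does not make a one-arm model a test of effect modification.

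**Conclusion.** The mismatch between stated aim and described method holds. As written, the predictor analysis gives prognostic factors after ULT cessation. Reading them as effect modifiers requires T2T risk to be low and flat across the features, and the protocol neither states nor tests that.

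The size of any misreading cannot be taken from the documents. The contrast between a T2S odds ratio of 1.8 and a constant 8-point difference rests on assumed stratum rates that average to the planning rates. Overfitting is possible rather than established, with a limiting count of about 17, 50 or 26 depending on the outcome definition.

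Severity is minor. The work is secondary and labelled exploratory, and the primary comparison is unaffected.

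**What to change.** 1. Call the T2S-only model prognostic in Outcomes {12} and the Discussion, and do not present its predictors as effect modifiers.
2. Prespecify a very short list of baseline features available in both arms. The factors named in the Discussion are natural candidates if recorded at baseline in both arms: serum urate on ULT, BMI, age at onset and ULT duration. Samples from the optional sub-study do not qualify, because they are taken only from T2S patients at one site.
3. For these features, fit the primary outcome in all randomised patients with a treatment-by-feature term, one feature at a time or with penalisation. Report risk differences with intervals across levels of each feature, as exploratory.
4. Replace the answer in {20b} with a reference to this analysis.
5. For the T2S model, define failed withdrawal, limit or penalise the candidate list, and repeat every selection step inside each cross-validation fold.

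The cost is wording and analysis time, with no new data if the features are already recorded in both arms. The downside is imprecision: with about 22 events expected across both arms, intervals for the interaction will be wide and a null result will say little. If the both-arm analysis is not wanted, step 1 alone, with effect modification dropped from the aims, removes the inconsistency.

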### Participant timeline {13}

During follow-up, three hospital visits are scheduled at the outpatient clinic, at baseline, month 12 and month 24 for both treatment strategy groups. For patients randomized to the T2S discontinuation group, 2 weeks after complete ULT cessation an extra blood sample is obtained and a telephone consult is scheduled one week later to discuss results and make sure patients indeed stopped the ULT (Fig. 2). Questionnaires are sent monthly (gout flare questionnaire) and three monthly (other questionnaires).

**Fig. 2 Fig2:**
[figure not shown]
Participation timeline

### Sample size {14}

The null hypothesis is that no statistical difference is found between the continued T2T approach and the T2S discontinuation approach. Since the T2S group receives less intensive treatment, the superiority of the T2S discontinuation approach in terms of efficacy is considered unlikely and also irrelevant. After all, one would prefer the less intensive treatment as long as the more intensive treatment is not clearly superior, regardless of whether the less intensive treatment is equally effective or superior. Therefore, we use a one-sided test to achieve the same power to show the superiority of continued T2T with a smaller study size compared to a two-sided test with the same alpha.

Based on earlier studies and on unpublished data from our own cohort (2400 gout patients from Sint Maartenskliniek, Radboudumc and Rijnstate) we estimate that 8% of gout patients following the treat-to-target strategy experience at least 1 gout flare during the 2-year follow-up and 4% of patients are not in remission in the last 6 months of the 24-month follow-up. For the patients in the treat-to-symptom group, less data is available, but we estimate that 12% are not in remission in the last 6 months of the follow-up time, based on the 5 smaller cohort studies included in the review of Beslon et al [11].

Using alpha 0.05, power 1-beta 0.80, one-sided superiority testing with a two proportion *z* test, and expected proportion of patients not fulfilling the adapted preliminary remission criteria for gout domains during the last 6 months of the study of 0.04 and 0.12 in the T2T strategy and control group T2S strategy (difference 0.08, number needed to harm, number needed to harm, NNH, 12), 278 analysable patients are needed. Accounting for 10% dropout, 310 patients will be included. If during follow-up dropout turns out to be lower (based on incidence density of dropout/patient-years), fewer patients will be included.

Only when superiority is not shown, non-inferiority (NI) of T2S compared to T2T will also be tested (using a NI margin of 8%, based on the NNH of a maximum of 12). Assuming 278 evaluable patients, point estimates for the primary outcome of 0.04 and 0.05 in the intervention and control group, and one-sided alpha of 5%, the power for proclaiming non-inferiority will be around 87%. However, we are aware of a higher risk of a false-positive result, also because this secondary analysis uses an opposite hypothesis of the original superiority hypothesis, therefore the non-inferiority analysis is considered an exploratory secondary analysis.

The NI margin is just like the difference in the superiority analysis based on the notion — developed together with patient partners — that a lower limit of NNH of 12 (not obtaining or loss of gout remission) balances nicely with the numbers needed to benefit of between 2 and 4 of not needing daily ULT pills for up to 2 years. In other words, a treatment effect smaller than an 8% point difference is not considered worthwhile compared to the burden of taking the medication.

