### Trial design {8}

The GO TEST Finale study is an investigator-initiated pragmatic, multicentre, two-arm, randomized, open-label, superiority treatment strategy trial in gout patients with disease remission ≥ 12 months while using ULT (allopurinol, benzbromarone and/or febuxostat). Participants are randomized 1:1 to either the T2T ULT continuation strategy group or the T2S discontinuation strategy group and are followed for 24 months.

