#### Secondary outcomes

Only when superiority cannot be demonstrated, non-inferiority testing will take place exploratory of the treat-to-symptom strategy compared to the treat-to-target strategy by calculating a confidence interval using the Miettinen and Nurminen method [30].The between-group difference in the incidence (cumulative incidence and incidence density rate) of gout flares during the follow-up period of 24 months.

Cumulative flare incidence is expressed as a proportion of the number of patients experiencing a flare at any time during the follow-up period. This is calculated separately for both groups and will be described by means of descriptive statistics as *n* (%). These proportions are compared using a chi-squared test or Fisher’s exact testThe proportion of participants that require reintroduction of ULT in the T2S group during the 24-month follow-up period.

The proportion of the number of patients in the T2S group in which the ULT is restarted will be expressed as n (%).The between-group difference in SU change during the total follow-up time and particularly at baseline and at the end of follow-up at 24 months.

Serum urate at baseline serum urate, 2 weeks after ULT discontinuation, month 12 and month 24 will be described as mean and 95% confidence intervals (CI). The difference from baseline measurement will also be described by the mean and 95% CI. A difference between the two groups will be compared with an independent *t*-test or Mann-Whitney test.To evaluate the between-group difference in Patient-Reported Outcome Measures (PROMs), by three monthly analysing the EQ-5D-5L questionnaire, functioning by using the Health Assessment Questionnaire Disability Index (HAQ-DI), numeric rating scale (NRS) for pain and NRS global health

Descriptive statistics in the form of mean and 95% CI will be used. The difference from baseline will also be presented using the mean and 95% CI. The difference in change in EQ-5D-5L, HAQ-DI, NRS pain and NRS global health between the groups will be analysed by an independent t-test or Mann-Whitney test.To assess the between-group difference in types and frequency of adverse events, with a special focus on change in renal function (CKD-EPI) and incidence of cardiovascular events during the follow-up period of 24 months.

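### The stated non-inferiority power of about 87% is not the power of the Miettinen-Nurminen interval named for that analysis, which is about 82%

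*Protocol article*

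**What the plan says.** Sample size {14} makes non-inferiority a conditional step: "Only when superiority is not shown, non-inferiority (NI) of T2S compared to T2T will also be tested". The margin is set "using a NI margin of 8%, based on the NNH of a maximum of 12". The power statement rests on these inputs: "Assuming 278 evaluable patients", "point estimates for the primary outcome of 0.04 and 0.05 in the intervention and control group", and "one-sided alpha of 5" per cent. From them the article concludes that "the power for proclaiming non-inferiority will be around 87" per cent. It does not name the formula. The same section accepts a raised risk of a false-positive result and classes the analysis as exploratory and secondary.

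The method of analysis is given elsewhere, under Statistical methods for primary and secondary outcomes {20a}, Secondary outcomes: non-inferiority will be assessed "by calculating a confidence interval using the Miettinen and Nurminen method". Trial design {8} gives the allocation: "Participants are randomized 1:1 to either the T2T ULT continuation strategy group or the T2S discontinuation strategy group".

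**The concern.** A planning power should describe the analysis that will be run. A Miettinen-Nurminen interval inverts a score test, so its variance is computed from rates constrained to differ by exactly the margin. When the expected rates are 4% and 5% and the margin is 8 points, the constrained rates lie much further apart, and their variance is clearly larger than the variance at the observed rates. A power worked out with the ordinary unconstrained variance will then be too high for the named method.

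If superiority of T2T is not shown, this is the analysis that could support T2S. A reader weighing a failed non-inferiority result would use the stated power to judge how informative that failure is.

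**Working it through.** **Inputs.** 278 evaluable patients, rates 0.04 (T2T) and 0.05 (T2S), margin 0.08 on the difference T2S minus T2T, one-sided 5% (z = 1.645): all from Sample size {14}. Allocation 1:1 from Trial design {8}, hence 278/2 = 139 per arm. Method from {20a}, Secondary outcomes. The one-sided 5% corresponds to the upper limit of a two-sided 90% interval.

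**Step 1: the plan's own figure.** With the unpooled (Wald) variance:

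- SE = √[(0.04 × 0.96 + 0.05 × 0.95)/139] = √(0.0859/139) = 0.02486
- Power = Φ[(0.08 − 0.01)/0.02486 − 1.645] = Φ(1.171) = 87.9%

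A pooled variance at 0.045 gives SE = √(2 × 0.045 × 0.955/139) = 0.02487 and again 87.9%. Exact enumeration of the Wald rule over all pairs of Binomial(139) counts gives 87.1%. The stated figure is therefore reproduced by a Wald-type calculation.

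**Step 2: the named method, by approximation.** For expected rates 0.05 and 0.04, the maximum-likelihood rates constrained to a difference of 0.08 are 0.1054 and 0.0254.

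- SE₀ = √[(0.1054 × 0.8946 + 0.0254 × 0.9746)/139] = 0.02927, against 0.02486 unconstrained
- Power = Φ[(0.08 − 0.01 − 1.645 × 0.02927)/0.02486] = Φ(0.879) = 81.0%

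**Step 3: the named method, exactly.** For each pair of counts, compute z = (0.08 − d)/√V. Here d is the observed difference, and V is the constrained variance times N/(N − 1) = 278/277. Non-inferiority is declared when z > 1.645. Summing the binomial probabilities at 0.05 and 0.04 gives **82.2%**.

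**One outcome where the two rules differ.** Take 9/139 on T2S and 4/139 on T2T, so d = 0.0360.

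- Wald: SE = 0.02523, upper limit 0.0360 + 1.645 × 0.02523 = 0.0775, below 0.08, so non-inferiority is declared.
- Miettinen-Nurminen: constrained rates 0.1007 and 0.0207, √V = 0.02829, z = (0.08 − 0.0360)/0.02829 = 1.556, below 1.645, so it is not declared.

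**Step 4: other readings.**

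| Rule, 139 per arm, one-sided 5% | Power |
|---|---|
| Wald, exact | 87.1% |
| Newcombe, exact | 83.7% |
| Miettinen-Nurminen, exact | 82.2% |
| Wald with continuity correction, exact | 81.0% |

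At the boundary of the null hypothesis (0.12 against 0.04), the exact one-sided error is 6.1% for Wald and 4.7% for Miettinen-Nurminen. Part of the higher Wald power comes from exceeding the nominal 5%.

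**Step 5: the conditional step.** At 0.04 and 0.05 the one-sided pooled z test for superiority rejects with probability 11.6%. The probability that superiority is not shown and Miettinen-Nurminen non-inferiority is shown is 80.7%. Given that superiority is not shown, non-inferiority is shown with probability 80.7/88.4 = 91.3%.

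**The case against.** The strongest reply is that this changes nothing in the design. The trial is sized on superiority, non-inferiority is labelled exploratory, and no sample size, margin, test or decision rule depends on the 87%. That stands, and it sets the severity.

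A second reply is that the planned inclusion is 310. If all 310 were evaluable (155 per arm), Miettinen-Nurminen power would be 85.9%, close to the stated figure. But the power statement assumes 278 explicitly, and the same section allows fewer inclusions if dropout is low. This reply does not rescue the figure.

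A third is that the article names no formula, so the use of Wald is an inference from the match. That also stands. A reader might infer that nothing but an unpooled Wald interval yields 87%; the pooled approximation comes equally close. The point does not depend on the source of the figure, only on the named method not giving it.

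A reader might go further and argue that the conditional step is itself an error, because it could leave a superiority claim standing with no comparison against the 8-point margin. The documents do not support that. The article conditions the non-inferiority test; it does not bar reporting the difference and its interval. Superiority and Miettinen-Nurminen non-inferiority would both hold in only 82.2 − 80.7 = 1.5% of trials at 4% against 5%, so the condition hides almost no non-inferiority result. Nor is 80.7% a correction of the stated 87%. It is a joint probability, and the article does not say whether its power is joint, conditional or unconditional.

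**Conclusion.** The concern holds as a minor arithmetic mismatch within the article. On the stated inputs, the named analysis has a power of about 82%, not about 87%, so the chance of missing non-inferiority is about 18% rather than 13%.

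The result assumes 139 evaluable patients per arm, true rates of exactly 0.04 and 0.05, and an interval at the one-sided 5% level given in the sample size section. The methods section states no confidence level; a two-sided 95% interval would give 71%. Because counts are discrete, exact power moves in small jumps (83.4% at 140 per arm), so about 82% is the right precision.

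It does not follow that the trial is underpowered for its primary question, or that the non-inferiority method, the margin or the conditional order is wrong.

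**What to change.** In Sample size {14}, restate the non-inferiority power as about 82%, and say that it refers to the Miettinen-Nurminen interval at a one-sided 5% level (two-sided 90%) with 139 evaluable patients per arm. Optionally add that the joint probability of superiority not being shown and non-inferiority being shown is about 81% at the same rates. The cost is one corrected figure and a short clause. Sample size, data collection and the planned analyses stay as they are; the only consequence is a slightly less favourable stated power.
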